### Demographic data collection

Demographic characteristics of all participants including age, gender, educational level, as well as medical history, medication list, and comorbidities will be documented.

### Neuropsychological assessment

A set of neuropsychological tests will be used to assess cognitive function and behavior of all the participants, and their activities of daily living will also be measured. The assessments will be performed at baseline, 4-week treatment, and 4-week post-treatment follow-up.

The Chinese version of the Montreal Cognitive Assessment Basic (MoCA-B) is a cognitive function screening tool tailored for individuals with low educational attainment, demonstrating high cultural adaptability (Chen et al., 2016; Julayanont et al., 2015). The total score is 30 points, with a score of ≥ 26 indicating normal cognitive function and a score of ≤ 26 suggesting impaired cognitive function. The cutoff scores for identifying MCI are adjusted according to the number of years of education: ≤ 19 points for those with ≤ 6 years of education, ≤ 22 points for those with 7-12 years of education, and ≤ 24 points for those with > 12 years of education.

The Rivermead Behaviour Memory Test (RBMT) is a behavioral memory assessment tool developed by the Rivermead Rehabilitation Centre in Oxford, England. It primarily evaluates patients’ memory function and consists of 12 items (Wilson et al., 1989). The total score is 24 points. The grading standards are as follows: 0–9 points indicate severe memory impairment, 10–16 points indicate moderate impairment, 17–21 points indicate mild impairment, and 22–24 points indicate normal memory function.

Modified Barthel Index (MBI) is used to assess the patient’s activities of daily living, including 10 items, including grooming, bathing, eating, toileting, and dressing (Mahoney and Barthel, 1965). The scoring standard is as follows: 100 were completely independent; 95–75 were classified as mild dysfunction; 70–50 were classified as moderate dysfunction; 50–25 were classified as severe dysfunction and obvious life dependence; ≤ 20 was totally dependent in life.

### Event-Related Potential

The visual P300 test will be conducted using the Chinese NianTong 32-channel ERP detection system. The test procedure employs the visual “oddball” paradigm. Stimulus materials are programmed using E-prime 3.0 software, with the deviant stimulus being a “red square” (accounting for 20%) and the standard stimulus being a “blue square” (accounting for 80%). These two different stimulus images are randomly presented on an LCD display, with a stimulus presentation time of 500 ms and an inter-stimulus interval of 1,000 ms. The target stimulus appears 40 times with a probability of 20%. A black background is used uniformly to enhance contrast and reduce visual fatigue. The subject is required to respond to the deviant stimulus each time (by clicking the left mouse button) (Figure 3). The test duration is approximately 10 min. Data acquisition is performed using eConScan_Aio software, with an AC sampling mode and a sampling frequency of 1,000 Hz to collect the raw EEG signals. The impedance between the electrodes and the subject’s skin was consistently maintained below 5 kΩ.

**FIGURE 3 F3:**
[figure not shown]
Visual P300 test behavioral experiment paradigm.

The analysis indicators generated after data processing include the P300 latency and amplitude. The P300 latency refers to the time interval from the onset of the stimulus signal to the peak of the waveform. The P300 amplitude is measured as the vertical distance (i.e., the peak value) from the waveform peak to the baseline, using the bilateral mastoids as the reference. The P300 component exhibits a near-central distribution on the scalp, primarily at the electrodes Fz (midline frontal site), Cz (midline central site), and Pz (midline parietal site), which are the main locations for P300 distribution. During data analysis, the P300 amplitude and latency at the Fz, Cz, and Pz electrodes are analyzed.

### Outcomes

The primary outcome is the MoCA-B score. Secondary outcomes include RBMT, MBI, P300 latency and amplitude. Any adverse events occurring during the intervention period, such as dizziness, pain, skin redness, and itchiness, will be reported by research assistants and managed by experienced physicians. We will assess the causality between adverse events and the treatment, as well as the severity of the adverse events. Serious adverse events will be reported to the ethics committee.

### Sample size calculation

The sample size was calculated using Power Analysis and Sample Size software version 15.0 (NCSS, LLC). The Factorial analysis of variance test is used for the sample size calculation of four groups. By referring to the previous literature (Wang et al., 2022). on rTMS or taVNS in the treatment of MCI, rTMS stimulation MoCA-B score is 16; taVNS stimulation MoCA-B score is 18; we estimate that the sham group MoCA-B score is 14 and the combined stimulation group MoCA-B score is 22. The target effect size is with 80% power (β = 0.20) and a type I error of 5% (α = 0.05). Considering a dropout rate of 10%, a total of 88 participants is necessary. In this study, we intend to recruit 88 participants, with 22 participants in each group.

### Quality control and quality assurance

At least three dementia specialists will work together to examine the participants and provide a diagnosis for each participant. All data will be monitored and reviewed by the principal investigator or research coordinators. Training will be provided to all researchers. Consistency coefficients in scoring assessment scales between researchers should be no less than 0.85. Data entry will be verified by a second researcher in the team. To protect participant confidentiality, only supervisors, researchers of this study, and the ethics committee will be authorized to access the personal information and medical records of the participants.

### Statistical methods

In this study, statistical analyses will be conducted using IBM SPSS Statistics 26. We will follow the intention-to-treat (ITT) principle for the primary analysis. For participants with partially missing outcome data (e.g., missed follow-up assessments), we will apply multiple imputation using chained equations under the assumption of data missing at random (MAR). Sensitivity analyses will be conducted using both complete-case analysis and per-protocol sets to assess robustness. Given the inclusion of multiple secondary outcomes (RBMT, MBI, P300 latency/amplitude), we will apply Bonferroni correction to adjust for multiple testing. Specifically, the significance threshold for secondary outcomes will be set as 0.0125. The study employs a 2 × 2 factorial design with rTMS (yes/no) and taVNS (yes/no) as independent factors. To examine the main effects and interaction effects of rTMS and taVNS on outcomes, we will use two-way repeated-measures ANOVA or mixed-effects models, depending on the distribution and structure of the data. For longitudinal outcomes measured at T0, T1, and T2, we will fit linear mixed-effects models (LMMs) with fixed effects for group, time, and their interaction, and a random intercept for participants to account for within-subject correlation. Additionally, we will explore including baseline covariates such as age, sex, and baseline cognitive score (e.g., baseline MoCA-B) in the models to improve precision and control for potential confounding. A *P* < 0.05 will be considered statistically significant.

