Throughout the trial, participants will be requested to actively report adverse events (AEs), including but not limited to: skin irritation/erythema, dizziness, transient palpitations, or nausea potentially associated with taVNS; headache, scalp discomfort, tinnitus, or seizure-like episodes potentially associated with rTMS. Each reported AE will be documented in the participant’s case report form (CRF). In the event of a serious AE (SAE) deemed causally related to the intervention, the subject will be withdrawn from the trial and referred for appropriate medical care by the protocol-mandated SAE management algorithm.

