### Ethics and dissemination

This study protocol has been approved by the Ethics Review Committee of Shanghai Tongren Hospital (No. 2021-047-01). Study-related information will be provided by the Rehabilitation Department of Shanghai Tongren Hospital. The purpose, objectives, inclusion criteria, and procedures of the research will be explained in detail. The research team will offer face-to-face consultations to all potential participants and their guardians to address any questions they may have prior to signing the informed consent forms. Written informed consent will be obtained from all participants. Participants are allowed to withdraw from the study at any time, and reasons for withdrawal will be documented. The results of this study will be published in peer-reviewed journals.

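### The planned sensitivity analyses do not examine departures from missing at random, and the related-SAE withdrawal rule can lose outcomes that the ITT analysis should keep

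*Protocol article*

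**What the plan says.** On the analysis set, Statistical methods says: "We will follow the intention-to-treat (ITT) principle for the primary analysis". Participants whose outcomes are partly missing are handled by multiple imputation with chained equations, with MAR as the declared assumption. The variables in the imputation model are not listed. On robustness: "Sensitivity analyses will be conducted using both complete-case analysis and per-protocol sets to assess robustness". The article names no analysis that departs from MAR.

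On withdrawal, Interventions says: "In the event of a serious AE (SAE) deemed causally related to the intervention, the subject will be withdrawn from the trial". It does not say whether the T1 and T2 assessments still take place for that participant. The same section has reported adverse events recorded in the case report form. Ethics and dissemination adds: "Participants are allowed to withdraw from the study at any time, and reasons for withdrawal will be documented".

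The Sample size calculation assumes 10% dropout, 88 participants (22 per group), and MoCA-B scores of 14 (sham), 16 (rTMS), 18 (taVNS) and 22 (combined). No standard deviation is given.

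**The concern.** A sensitivity analysis for missing data should vary the assumption on which the primary analysis leans. Here that assumption is MAR: given what the model contains, participants who leave would have scored like similar participants who stay. If people leave because treatment is not helping or is poorly tolerated, and the model does not capture this, MAR imputation gives them scores that are too good.

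Neither named check addresses this. For missing outcomes, complete-case analysis needs missingness that is completely random or depends only on covariates in the model, which is no weaker than MAR. Per-protocol analysis changes who is analysed and which question is answered. All three could agree and all could be wrong in the same direction, and the agreement would be read as reassurance.

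The SAE rule adds a route by which outcomes can be lost for a reason tied to treatment. Its trigger is a causal link to the intervention, so such losses should fall mainly in the three arms with active stimulation. ITT calls for outcomes to be collected as randomised, whether or not stimulation continues. At stake is some overstatement of the active-arm effects that the planned checks would not reveal.

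**Working it through.** **Inputs from the documents.** Means 14, 16, 18 and 22; 22 per group; 10% dropout. The planned combined-versus-sham difference is 22 - 14 = 8. The planned interaction is (22 - 18) - (16 - 14) = 2. The planned main effects are [(16 - 14) + (22 - 18)]/2 = 3 for rTMS and [(18 - 14) + (22 - 16)]/2 = 5 for taVNS.

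**The plan's own figure.** The point rests on no stated result, only on the dropout allowance. That step is arithmetically possible: 80 x 1.1 = 88, or 79/0.9 = 87.8, rounded up to 88. The base number cannot be reproduced without a standard deviation. Ten per cent of 88 is 8.8 participants, about 2 per group.

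**Bias in an arm mean.** Bias = missing fraction x shift, where the shift is how much worse the missing outcomes truly are than MAR imputation assumes. At 10% missing this is 0.1 point per point of shift. With exactly 2 of 22 missing it is 2/22 = 0.091.

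**Scenario: dropouts in all active arms truly end at the sham level of 14 but are imputed at their arm's mean.**
- Combined: 0.10 x (22 - 14) = 0.8
- taVNS: 0.10 x (18 - 14) = 0.4
- rTMS: 0.10 x (16 - 14) = 0.2
- Combined versus sham overstated by 0.8 of 8 (10%)
- Interaction overstated by 0.8 - 0.4 - 0.2 = 0.2 of 2 (10%)
- rTMS main effect overstated by [0.2 + (0.8 - 0.4)]/2 = 0.3 of 3 (10%)
- taVNS main effect overstated by [0.4 + (0.8 - 0.2)]/2 = 0.5 of 5 (10%)

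**Worst case: only the combined arm is affected.** The interaction is overstated by 0.8 of 2.

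**Do the checks show it?** Simulation of combined minus sham, 22 per arm, with assumed SD 3, assumed baseline correlation 0.6 and 10% missing in active arms only:

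| Shift in missing values | True ITT difference | Complete-case | MAR imputation | MAR minus true |
|---|---|---|---|---|
| 0 | 8.01 | 8.02 | 8.02 | 0.01 |
| 2 | 7.79 | 7.99 | 7.99 | 0.20 |
| 4 | 7.64 | 8.04 | 8.04 | 0.40 |
| 8 | 7.21 | 8.00 | 8.01 | 0.80 |

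Complete-case and MAR imputation agree on every row and both miss the shift. Per-protocol was not simulated; the point about it rests on its change of population.

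**How many participants the SAE rule might affect.** No rate is given. For an assumed related-SAE risk of 0.5% to 5% among the 3 x 22 = 66 participants with active stimulation, the expected number is 66 x 0.005 = 0.33 to 66 x 0.05 = 3.3. The chance of at least one is 28% to 97%.

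**The case against.** The strongest reply is that this is an omission from a condensed article. A delta-adjusted or reference-based analysis often sits in a statistical analysis plan, and none is shown here. The article does not claim that its two checks probe MAR. That limits the finding to what is stated, but it does not remove it: the article itself selects these two analyses as its robustness check, directly after declaring MAR.

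A reader might infer that the SAE rule creates informative missingness and contradicts ITT. The documents do not support that. The triggering event is recorded, so missingness can be MAR given arm, SAE and earlier scores if these enter the imputation model. A withdrawn participant can also be imputed and stay in the ITT set, and the article does not say that assessments stop. In practice, conditioning may help little: if the rule ended collection for every such participant, there would be no post-event scores from which to learn. The wording is therefore ambiguous and in tension with ITT, no more.

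Nor is it a fault that the checks cannot test MAR, since no analysis of observed data can. The accurate complaint is that departures from MAR are not explored.

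The size can also be oversold. Quoting a 40% bias in the interaction (0.8/2) requires combined-arm dropouts to lose all 8 points while dropouts in the single-stimulation arms lose nothing. Bringing the planned interaction to zero through 2 missing of 22 in the combined arm would take a shift of 2 x 22/2 = 22 points on a 30-point scale. Losing significance would take less, but how much less depends on a standard deviation that the article does not give.

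**Conclusion.** The concern holds in a limited form. The named sensitivity analyses do not examine departures from MAR, so their agreement with the primary result would not show robustness to non-random dropout. The related-SAE rule, followed as written, can end outcome collection for a treatment-related reason and should be reconciled with the ITT statement.

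The effect is modest: about 0.1 point per point of shift at 10% missing, or about 10% of each planned contrast if all active-arm dropouts truly end at the sham level. This rests on the article's planned means and dropout rate and on an assumed shift; nothing in the article shows that dropouts do worse. Related SAEs should account for few losses, so ordinary dropout matters more. The change is worth making because it is cheap and improves a stated method.

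**What to change.** 1. In Statistical methods, add a delta-adjusted (tipping-point) or sham-reference multiple imputation for MoCA-B, at the time point or points used for the primary contrast. A delta range of 0 to 8 points would span the planned combined-versus-sham difference. Let delta differ between active arms, so that the case where only the combined arm is affected is covered.
2. Keep complete-case and per-protocol as supplementary analyses.
3. State that the imputation model includes arm, earlier scores and adverse event status.
4. Reconcile Interventions with Statistical methods by separating discontinuation of stimulation from withdrawal from the trial. Participants who still consent would have T1 and T2 assessed and be analysed in the ITT set. No change to when stimulation stops is proposed.

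The cost is a little more analysis code, a check on how the adjusted imputation will be run alongside the named software, a few sentences of protocol text, and follow-up visits for a few participants who are off stimulation.

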### ERP-P300

Data processing will be conducted using MATLAB R2022b. The EEG raw data preprocessing will be performed using the EEGLAB toolbox. The preprocessing steps mainly include: localizing electrodes, removing unused electrodes, referencing, filtering, segmenting, and baseline correcting the data, as well as removing artifacts and performing independent component analysis (ICA) (Zhuang et al., 2023). After preprocessing the ERP data, the amplitude and latency of the P300 wave will be analyzed at the Fz, Cz, and Pz electrodes.

The significance level for statistical analysis will be set at 5% (*P* < 0.05). The researchers conducting the data analysis will be blinded to the allocation and interventions.

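### P300 latency and amplitude fall under two significance thresholds, 0.0125 and 0.05, and 0.0125 is right only if each measure yields a single test

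*Protocol article*

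**What the plan says.** The Outcomes section gives the list: "Secondary outcomes include RBMT, MBI, P300 latency and amplitude". The Statistical methods section places the same outcomes in one corrected family: "Given the inclusion of multiple secondary outcomes (RBMT, MBI, P300 latency/amplitude), we will apply Bonferroni correction to adjust for multiple testing". It then fixes the level: "Specifically, the significance threshold for secondary outcomes will be set as 0.0125". The last sentence of that section says that P < 0.05 "will be considered statistically significant", without limiting this to the primary outcome.

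The ERP-P300 section, which follows, states that "the amplitude and latency of the P300 wave will be analyzed at the Fz, Cz, and Pz electrodes". Its next paragraph reads "The significance level for statistical analysis will be set at 5" per cent (P < 0.05). The text below Figure 3 in the Event-Related Potential section repeats the three sites: "During data analysis, the P300 amplitude and latency at the Fz, Cz, and Pz electrodes are analyzed". The article names no lead electrode, no average over electrodes, no joint model across electrodes and no correction across them.

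**The concern.** Two decision rules apply to the same outcomes. An analyst who follows Statistical methods judges P300 at 0.0125. One who turns to the section headed ERP-P300 judges it at 0.05. With P = 0.03, the first reports no significant effect and the second reports one. P300 is the only EEG-derived outcome listed, and the Introduction says that EEG is included to explore the mechanism of the combined therapy, so the neurophysiological conclusion could turn on which paragraph is followed.

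A second, conditional question concerns the divisor. The figure 0.0125 counts latency and amplitude once each, while both are analysed at three sites. Unless the three sites are reduced to one test, the number of tests exceeds the number that the threshold was built for.

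**Working it through.** **Inputs.** Overall level: "a type I error of 5% (α = 0.05") in Sample size calculation. Secondary threshold 0.0125 and its family: Statistical methods. Four secondary outcomes: Outcomes. Second level of 0.05 and three electrodes: ERP-P300; the electrodes also in Event-Related Potential. The correlation between electrodes is not given, so a range is shown. All error rates below are for one effect at one visit.

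**1. The plan's own figure.** Bonferroni threshold = α/m. With m = 4, 0.05/4 = 0.0125, an exact match. With P300 counted as one outcome, m = 3 gives 0.05/3 = 0.0167, which does not match. The divisor is not written down, but 4 reproduces the figure.

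**2. Four tests, all at 0.0125.** Bound: 4 × 0.0125 = 0.050. If independent: 1 − 0.9875⁴ = 0.049. The intended control holds.

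**3. Four tests, with the 5% rule governing P300.** RBMT and MBI at 0.0125, latency and amplitude at 0.05, one test each.
- Bound: 2 × 0.0125 + 2 × 0.05 = 0.125.
- If independent: 1 − 0.9875² × 0.95² = 0.120.

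**4. Separate electrode tests, all at 0.0125.** Number of tests: 2 + 2 × 3 = 8.
- Bound: 8 × 0.0125 = 0.100.
- If independent: 1 − 0.9875⁸ = 0.096.
- With correlated electrodes: a simulation of 1,000,000 draws under the null used normal test statistics, an equal correlation among the three electrodes within each measure, and independence between latency, amplitude, RBMT and MBI.

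| Assumed electrode correlation | All eight tests at 0.0125 | Six P300 tests at 0.05, RBMT and MBI at 0.0125 |
|---|---|---|
| 0 | 0.096 | 0.283 |
| 0.5 | 0.090 | 0.254 |
| 0.7 | 0.082 | 0.227 |
| 0.9 | 0.068 | 0.180 |
| 1 | 0.049 | 0.120 |

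The last column combines both problems; its bound is 2 × 0.0125 + 6 × 0.05 = 0.325.

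**5. Threshold for eight tests.** 0.05/8 = 0.00625; bound 8 × 0.00625 = 0.050; if independent, 1 − 0.99375⁸ = 0.049. This covers one effect at one visit. Statistical methods also plans two main effects and an interaction, with post-baseline visits T1 and T2, and 0.00625 does not cover those.

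**The case against.** The best defence of the two levels is that 5% is the general nominal level and that the specific rule for secondary outcomes overrides it. The 5% sentence in the ERP-P300 section names no outcome. It stands in a closing paragraph beside a statement on blinding of the analysts, which applies to the whole trial. This is a reasonable guess at the intention. But the article does not say it, and the sentence sits under the P300 heading, where an analyst would look for the P300 rule. The ambiguity for P between 0.0125 and 0.05 stands.

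On the divisor, the defence is stronger. A reader might infer that 0.0125 is an arithmetic error, or that the multiplicity control certainly fails because eight tests will be run. The article supports neither. The division is correct for the four named outcomes. Both P300 passages say only that the measures are analysed at three sites, not that each site gets its own significance test. Repeated-measures ANOVA or a mixed model, both named in Statistical methods, could carry electrode as a within-subject factor and give one test per measure. How the sites are combined is also a detail that an article may leave to a fuller document. The inflation from separate tests is therefore conditional, and midline sites that record one component are likely to be correlated, which puts the figure below 9.6%.

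**Conclusion.** The conflict between 0.0125 and 0.05 for P300 is on the page and does not depend on how electrodes are handled. If the 5% rule were followed with one test per measure, the family-wise error bound for the secondary outcomes would be 12.5% (12.0% if independent) against the intended 5%.

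The divisor of 4 is valid if each P300 measure gives one test for one effect. If the three electrodes were tested separately at 0.0125, the bound would be 10%: 9.6% if independent, between 9.0% and 6.8% at assumed correlations of 0.5 to 0.9, and about 5% only at correlation 1. This part calls for clarification and is not a demonstrated failure of control.

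MoCA-B and the sample size are not touched. The matter is one of consistency in secondary outcomes and should be settled before the analysis.

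**What to change.** 1. In Statistical methods, state that 0.05 applies to the primary outcome (MoCA-B) only.
2. In ERP-P300, replace the 5% statement with 0.0125 for P300 latency and amplitude.
3. Prespecify one P300 test per measure, for example on the mean of Fz, Cz and Pz, or from one model with electrode as a within-subject factor. Name one contrast per secondary outcome. The family is then four tests and 0.0125 is correct. Report single-electrode results as descriptive.
4. If separate electrode tests are to stay confirmatory, use at most 0.05/8 = 0.00625 per effect and visit, and say how the factorial effects and visits are handled, since 0.00625 alone does not cover them.

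The first two items cost a sentence each. The third and fourth are design choices as well as wording: either single-electrode results lose confirmatory status, or the threshold becomes stricter. No change to recruitment, assessments or sample size follows.

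### A cheap improvement, not an error: Holm's step-down procedure over the same four secondary P values keeps the 5% family-wise error and never rejects less than the fixed 0.0125 cut

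*Protocol article*

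**What the plan says.** The Outcomes section names four secondary outcomes: "Secondary outcomes include RBMT, MBI, P300 latency and amplitude". For these, Statistical methods states that "we will apply Bonferroni correction to adjust for multiple testing" and that "the significance threshold for secondary outcomes will be set as 0.0125". No stepwise procedure is mentioned, so each secondary P value is compared with the same cut whatever the other three show.

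Three other statements bear on how the rule would be applied:

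- Statistical methods closes with a general criterion: "A *P* < 0.05 will be considered statistically significant". The ERP-P300 section likewise sets a 5% level and does not mention 0.0125.
- In the ERP-P300 section, "the amplitude and latency of the P300 wave will be analyzed at the Fz, Cz, and Pz electrodes", so each P300 measure yields three values.
- The factorial analysis is meant "To examine the main effects and interaction effects of rTMS and taVNS on outcomes", so each outcome can yield more than one P value.

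The article does not say which single P value per outcome the division by four refers to.

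**The concern.** Single-step Bonferroni is not the sharpest rule that gives the protection the authors want. Once one secondary outcome has passed 0.0125, at most three null hypotheses can still be true if that rejection is correct, and holding the rest to 0.0125 is stricter than 5% family-wise control needs. Under the written rule a secondary P value between 0.0125 and 0.05 is always non-significant, even when the other three outcomes are clearly established.

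At stake is power on the secondary outcomes in a trial of 88 participants that calls its own sample relatively small. The hypothesis is of a broad cognitive benefit, with EEG used to explore the mechanism. If it is right, several secondary outcomes would move together, and that is where a stepwise rule helps most. The primary MoCA-B analysis is not affected.

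**Working it through.** **1. The plan's figure.** Four outcomes (Outcomes section) and an overall level of 0.05 (Sample size calculation; Statistical methods) give 0.05/4 = 0.0125, which reproduces exactly. With four independent tests the family-wise error is 1 − (1 − 0.0125)^4 = 0.049.

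**2. Holm over the same four P values.** Order them from smallest to largest and compare with 0.05/4 = 0.0125, 0.05/3 = 0.0167, 0.05/2 = 0.025 and 0.05/1 = 0.05, stopping at the first failure.

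- *Never rejects less.* Every Holm threshold is at least 0.0125. A P value at or below 0.0125 passes its own step, and so do all smaller ones.
- *Controls the error at 5% under any correlation.* Suppose k of the four nulls are true. When the first true null is reached, at most 4 − k hypotheses have been rejected, so its threshold is at most 0.05/k. A false rejection therefore needs one of k null P values to be at or below 0.05/k, which has probability at most k × 0.05/k = 0.05.

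The same argument holds for any fixed family of m tests, with thresholds 0.05/m, 0.05/(m − 1), and so on.

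**3. Size of the gain.** The article gives no effect sizes, SDs or correlations for the secondary outcomes, so these inputs are assumptions: one normally distributed test statistic per outcome, correlation 0.3 between outcomes, and a standardised effect d = 0.6 wherever an effect is real. After 10% dropout, 88 × 0.9 = 79.2, or about 40 per level of each factor, and 22 × 0.9 = 19.8, or about 20 per cell.

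The shift of the test statistic is d × √(n/2). For 40 v 40 it is 0.6 × √20 = 2.683, and for 20 v 20 it is 0.6 × √10 = 1.897. The two-sided critical value at 0.0125 is 2.498. Bonferroni power is therefore 57.4% and 27.4%. Holm was simulated:

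| Real effects out of four | 40 v 40, Bonferroni to Holm | 20 v 20, Bonferroni to Holm |
|---|---|---|
| 1 | 57.4% to 57.5% | 27.4% to 27.5% |
| 2 | 57.4% to 59.7% | 27.4% to 28.7% |
| 3 | 57.4% to 62.6% | 27.4% to 30.2% |
| 4 | 57.4% to 66.9% | 27.4% to 32.4% |

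At 40 v 40 with all four effects real, the chance of declaring all four rises from 20% to 41%. The chance of at least one rejection is identical under both rules, because both start at 0.0125. No simulated data set had a Bonferroni rejection that Holm missed. Correlations of 0 and 0.5 give similar gains per outcome.

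**4. Sensitivity.** With all four effects real at 40 v 40, power goes from 40% to 47% at d = 0.5 and from 74% to 83% at d = 0.7. Starting instead from 80% power per outcome at 0.05, with correlations from 0 to 0.6, Bonferroni gives 62%. Holm gives 62% with one real effect, 64–65% with two, 67–68% with three and 71–73% with four. For an interaction contrast of 0.6 SD with 20 per cell, power goes from 12% to 13% (two real) or 14% (four real).

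**5. Error used.** With no real effects the family-wise error is the same under both rules, about 4.7–4.8% at correlation 0.3. With three real effects and one true null, it is 1.2% under Bonferroni and about 3% under Holm, still below 5%.

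**The case against.** The strongest reply is that nothing here is wrong. A pre-specified Bonferroni correction on secondary outcomes is valid and conservative, creates no false claim, and gives simultaneous confidence intervals that match the tests. This stands. A reader might infer that the plan contains an error, or that it gives away power for nothing. The documents support neither: the rule does what it claims for four P values, and the simpler intervals are a real if modest advantage.

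A second objection is that the plan yields more than four secondary P values. Two P300 measures at three electrodes plus RBMT and MBI make 2 × 3 + 2 = 8 variables, and three factorial effects each make 24 tests. Holm over 8 tests starts at 0.05/8 = 0.00625 and over 24 at 0.05/24 = 0.0021, so it could reject less than the written 0.0125. The arithmetic is right, but it compares Holm over one family with Bonferroni over another. Over the same family Holm still never rejects less. What stands is a condition: Holm has to order a defined list of P values, and 5% control over four tests holds only if each outcome supplies one named P value.

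Third, the general 5% statement and the one in the ERP-P300 section leave it unsettled whether the P300 outcomes are held to 0.0125 at all. If they are judged at 5%, they lose no power now. That also stands and should be settled in the same edit.

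Finally, a reader might expect the 10-point gain per outcome, or the doubling from 20% to 41%. Both need four real effects of equal size. The article gives no secondary effect sizes, and its Discussion cites a failure of taVNS to change P300 in healthy volunteers.

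**Conclusion.** The point holds as an optional, low-cost improvement. The fixed 0.0125 cut is valid, but over the same four P values Holm gives the same 5% family-wise guarantee under any correlation and never rejects less.

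At 40 v 40, d = 0.6 and correlation 0.3, the gain in power per truly affected outcome is about 0, 2, 5 and 10 percentage points with one, two, three and four real effects. It is smaller for 20 v 20 cell comparisons and smaller still for the interaction. These sizes rest entirely on assumed effects. The dominance of Holm does not, but it does require both rules to be applied to the same defined family.

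**What to change.** In Statistical methods, replace the fixed 0.0125 with wording such as: *The secondary outcomes will be tested with Holm's step-down procedure at a family-wise level of 5%, using one pre-specified P value per outcome. The ordered P values will be compared with 0.0125, 0.0167, 0.025 and 0.05, stopping at the first that fails.*

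Two things must accompany it:

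- Name the P value that each outcome supplies: the effect tested, the time point and, for P300, the electrode or a summary across electrodes. If the family is defined with m tests instead of four, use 0.05/m, 0.05/(m − 1), and so on.
- Make the 5% statement in the ERP-P300 section refer to this rule, and limit the general P < 0.05 sentence to analyses outside the secondary family.

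The change should be made before unblinding. It needs no extra participants, data or software, since Holm can be applied by hand to four P values. The costs are that simultaneous confidence intervals matching the tests are less simple than with Bonferroni (Bonferroni-level intervals can still be shown descriptively), and that more of the permitted 5% error is used when some effects are real.
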